# Aspiration sclerotherapy combined with pasireotide to improve reduction of large symptomatic hepatic cysts (SCLEROCYST): study protocol for a randomized controlled trial

**DOI:** 10.1186/s13063-015-0607-3

**Published:** 2015-03-07

**Keywords:** Hepatic cyst, Polycystic liver disease, Aspiration sclerotherapy, Somatostatin analogues, Pasireotide

## Abstract

**Background:**

Aspiration sclerotherapy is an effective therapeutic option for large symptomatic hepatic cysts. However, incomplete cyst reduction following aspiration sclerotherapy is frequently reported. Strong post-procedural cyst fluid secretion by cholangiocytes, which line the epithelium of the hepatic cyst, seems to be associated with lower reduction rates. Previous studies showed that somatostatin analogues curtail hepatic cyst fluid production. This trial will evaluate the effect of aspiration sclerotherapy combined with the somatostatin analogue pasireotide on cyst reduction. By combining treatment modalities we aim to improve cyst reduction leading to greater symptomatic relief and reduced rates of cyst recurrence.

**Methods/Design:**

This single center, randomized, double-blind, placebo-controlled clinical trial evaluates the additional effect of pasireotide when combined with aspiration sclerotherapy in patients with a large (>5 cm) symptomatic hepatic cyst. A total of 34 participants will be randomized in a 1:1 ratio. In the active arm, patients will receive pasireotide (long-acting release, 60 mg injection) two weeks prior to and two weeks following aspiration sclerotherapy. Patients in the control arm will receive placebo injections at corresponding intervals. The primary outcome is proportional cyst diameter reduction four weeks after aspiration sclerotherapy compared to baseline measurements, obtained by ultrasonography. As secondary outcomes, proportional volume reduction, recurrence, symptomatic relief and improvement of health-related quality of life will be assessed. Furthermore, safety and tolerability of the combination of pasireotide and aspiration sclerotherapy will be evaluated.

**Discussion:**

This trial aims to improve efficacy of aspiration sclerotherapy by a combined approach of two treatment modalities. We hypothesize that pasireotide will decrease fluid re-accumulation after aspiration sclerotherapy, leading to effective hepatic cyst reduction and symptomatic relief.

**Trials registration:**

This trial is registered with ClinicalTrials.gov (identifier: NCT02048319; registered on 6 January 2014) and EudraCT (identifier: 2013-003168-29; registered on 16 August 2013).

## Background

Hepatic cysts are fluid-filled cavities originating from congenital malformations of biliary duct cells. Isolated cysts occur at a prevalence of 2.5 to 18%, while polycystic liver disease (PLD) is infrequent [1-4]. Large or multiple hepatic cysts may cause symptomatic disease. Mass-related symptoms include abdominal distension, pain, postprandial fullness, nausea and dyspnea, collectively leading to a compromised health-related quality of life [5,6]. Treatment should be considered in all symptomatic patients [4,7]. Aspiration sclerotherapy (AS) is a minimally invasive procedure indicated for both solitary and dominant hepatic cysts in PLD. AS includes percutaneous drainage of cyst fluid with subsequent intracystic instillation of a sclerosing agent (such as ethanol or tetracycline) aiming to destroy the inner cystic lining of cholangiocytes [8,9]. However, the efficacy of AS is limited due to direct fluid re-accumulation following treatment [10]. Although re-accumulation is transient, strong fluid secretion is associated with lower efficacy rates leading to failure of symptom relief and the necessity to re-intervene [7,10,11].

Somatostatin analogues inhibit cyst fluid production [12]. Several randomized clinical trials demonstrated that somatostatin analogues (octreotide and lanreotide) decrease polycystic liver volume [13-15]. Pasireotide (SOM230) is a more potent somatostatin analogue compared to conventional somatostatin analogues as it has a broader binding profile and stronger affinity to its receptors [16,17]. We hypothesize that pasireotide administration reduces fluid re-accumulation following AS and therefore increases diameter reduction. We expect that inhibited re-accumulation results in effective symptomatic relief and reduced recurrence rates. To this end, we have designed a randomized, double-blind, placebo-controlled clinical trial to evaluate clinical efficacy of AS combined with pasireotide.

## Methods/Design

### Study aim

The primary objective of the SCLEROCYST trial is to evaluate the combined effect of AS and pasireotide on cyst diameter reduction. Secondary objectives are to determine symptomatic relief and cyst recurrence.

### Hypothesis

We hypothesize that administrating pasireotide curtails fluid re-accumulation following AS and thereby increases cyst diameter reduction.

### Study design and setting

The SCLEROCYST trial is a randomized, double-blind, placebo-controlled clinical trial. This single-center study is performed at the Radboud University Medical Center, Nijmegen, the Netherlands. Trial duration will be 30 weeks, consisting of a screening period of four weeks and a treatment period of 26 weeks (Figure 1).

**Figure 1 Fig1:**
[figure not shown]
**Study design of the SCLEROCYST trial.** AS, aspiration and sclerotherapy; INJ, injection of pasireotide or placebo; Q, assessment of GIS-, PLD- and SF-36 questionnaires; US, ultrasonography.

### Randomization and treatment allocation

A total of 34 patients will be randomized in a 1:1 ratio to receive either pasireotide or placebo. All patients will be subjected to AS. Randomization will be performed using block randomization with a block size of four. Included patients will be assigned a randomization number, corresponding to a treatment arm, concealed in a closed envelope. Access to treatment allocation will be restricted to research nurses who prepare and administer the injections. Both patients and treatment allocators will be unaware of the allocated treatment.

### Study population

All patients who are diagnosed with a symptomatic, hepatic cyst that meet the following eligibility criteria will be suitable for participation in this study.

#### Inclusion criteria

The inclusion criteria for this study are as follows:Aged between 18 and 70 years,Indication for treatment with AS, made upon diagnosis of a symptomatic, simple hepatic cyst exceeding 5 cm in diameter,The treated hepatic cyst must be solitary or dominant by nature; a dominant hepatic cyst is the largest cyst surrounded by multiple smaller cysts in patients with PLD andProvision of informed consent to participate.

#### Exclusion criteria

The aspiration sclerotherapy-related exclusion criteria are as follows:Suspicion of a complicated hepatic cyst (active cyst hemorrhage, rupture, or infection),Coagulopathy (international normalized ratio (INR) >2 or platelet count <80 × 10^9^/l) orSevere co-morbidity contraindicating anesthesia (ASA 4 classification).

The pasireotide treatment-related exclusion criteria are as follows:Known long QT syndrome and/or corrected QT interval (QTc) at screening >470 ms;Family history of long QT syndrome or idiopathic sudden death;Uncontrolled or significant cardiac disease including a recent myocardial infarction, congestive heart failure, unstable angina or sustained and/or clinically significant cardiac arrhythmias;Risk factors for torsades de pointes: hypokalemia, hypomagnesemia, hypocalcaemia, clinically significant bradycardia or high grade atrioventricular block;Concomitant disease that could prolong QT interval such as autonomic neuropathy, HIV, cirrhosis, uncontrolled hypothyroidism or cardiac failure;Use of anti-arrhythmic medicinal products or other substances known to lead to QT interval prolongation;Symptomatic cholecystolithiasis;Uncontrolled diabetes, defined as glycated hemoglobin (HbA1C) level >64 mmol/ml despite adequate therapy;Moderate to severe hepatic impairment defined by a Child-Pugh classification of more than six points;History of acute pancreatitis;Hypersensitivity to somatostatin analogues or any component of pasireotide orNon-malignant medical illnesses that are uncontrolled or whose control may be jeopardized by the treatment with the study therapy.

Further exclusion criteria are as follows:Pregnant or nursing women,Use of oral contraception or estrogen supplementation,Intervention (aspiration with or without sclerotherapy or surgical intervention) within six months prior to baseline,Treatment with somatostatin analogues within six months prior to baseline orAny current or prior medical condition that may interfere with the conduct of the study or the evaluation of its results in the opinion of the investigator.

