#### Screening visit (within four weeks prior to starting the trial)

Potential subjects with an indication for AS will be asked to participate. Informed consent will be obtained from all participants. Upon providing informed consent, each subject will be screened for eligibility during a separate screening visit performed within 28 days prior to the start of the trial. During this screening visit the following assessments will be made:obtain written informed consent;extensive medical history and physical examination;laboratory markers: potassium, calcium, magnesium, estimated glomerular filtration rate calculated by the Modification of Diet in Renal Diseases (MDRD) formula, platelets, INR, alanine aminotransferase (ALT), aspartate aminotransferase (AST), alkaline phosphatase (ALP), gamma-glutamyl transpeptidase (GGT), total bilirubin (TB), albumin and fasting blood sugar (FBS);urine pregnancy test in female patients with childbearing potential;electrocardiogram: frequency, QTc and atrioventricular conduction;ultrasonography: cyst diameter and volume measurement andquestionnaires: GIS-, PLD- and SF-36 questionnaire.

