#### Aspiration sclerotherapy (week two)

Patients will be admitted the day of AS. Prior to the intervention, adverse events in the previous two weeks will be assessed. Moreover, blood will be drawn to evaluate safety laboratory markers (potassium, magnesium, FBS, ALT, AST, TB and amylase). AS will be performed following standard procedure in both arms. Aspirated cyst fluid will be stored in our laboratory for future analyses.

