#### Second injection (week four)

Two weeks following AS (four weeks following the first injection) the patient will visit the outpatient clinic to receive the second injection. Cyst diameter will be assessed. All adverse events will be documented and blood will be obtained. If the following laboratory parameter levels are found, the second injection will not be administered:FBS >9.9 mmol/l;AST or ALT >5 × upper limit of normal (ULN);AST or ALT >3 × ULN with TB >2 × ULN oramylase >10 × ULN.

If the parameters fall within the margin of safety, the second injection will be administered.

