#### Follow-up visits (week six, 14 and 26)

Three follow-up visits will be planned at six, 14 and 26 weeks following the first injection (four, 12 and 24 weeks following AS). The researcher will document adverse events and blood will be drawn to assess safety laboratory markers (FBS, ALT, AST, ALP and GGT). The diameter of the treated cyst will be captured and cyst volume will be calculated. The primary endpoint of this study, mean proportional change (%) in cyst diameter at four weeks after AS, will be obtained during the first follow-up visit. Furthermore, abdominal symptoms and health-related quality of life will be measured using the GIS-, PLD- and SF-36 questionnaires.

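### The uncontrolled-diabetes exclusion sets its HbA1c threshold in a physically impossible unit, and HbA1c is not among the listed screening tests

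*Protocol article*

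**What the plan says.** Under Exclusion criteria, among the pasireotide-related items, the article lists "Uncontrolled diabetes, defined as glycated hemoglobin (HbA1C) level >64 mmol/ml despite adequate therapy".

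Under Screening visit, it says that "each subject will be screened for eligibility during a separate screening visit performed within 28 days prior to the start of the trial". The laboratory list for that visit opens with "laboratory markers: potassium, calcium, magnesium, estimated glomerular filtration rate calculated by the Modification of Diet in Renal Diseases (MDRD) formula, platelets, INR", continues with ALT, AST and ALP, and ends with "gamma-glutamyl transpeptidase (GGT), total bilirubin (TB), albumin and fasting blood sugar (FBS"). HbA1c is not in it.

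The other itemised blood panels do not contain HbA1c either. On the day of aspiration sclerotherapy they are "safety laboratory markers (potassium, magnesium, FBS, ALT, AST, TB and amylase"). At weeks 6, 14 and 26, "blood will be drawn to assess safety laboratory markers (FBS, ALT, AST, ALP and GGT").

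The section on pasireotide names transient hyperglycaemia as a common side effect and describes the product as a one-month depot. The only numerical glycaemic rule besides the HbA1c exclusion is in the section on the second injection, which withholds that injection if fasting blood sugar exceeds 9.9 mmol/l.

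**The concern.** An eligibility threshold has to be a number that a patient can fall above or below, and the screening visit has to produce the measurement. On the text, this criterion fails both tests. The unit is an amount per volume that no blood sample reaches, and the visit at which eligibility is decided does not list the test.

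What is at stake is mainly safety and the definition of the trial population. The drug is expected to raise glucose, and a depot injection cannot be taken back. If the HbA1c rule does not work, the first numerical glycaemic rule that can act on a patient is the one at week 4, after the first injection has been given at week 0. Fasting blood sugar is measured at screening and at week 2, but the document ties no numerical rule to those results.

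**Working it through.** **Step 1: the unit.** The threshold is a stated cut-off, so there is no derivation to reproduce. The question is whether 64 mmol/ml can occur. The documents give no molar mass for haemoglobin and no blood density. I assume 16 g/mmol (a single chain) to 64.5 g/mmol (the whole tetramer), and about 1 g of blood per ml.

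- Mass implied by the threshold = 64 mmol/ml × molar mass: 64 × 16 = 1,024 g/ml; 64 × 64.5 = 4,128 g/ml.
- Highest possible value if the whole ml were haemoglobin = 1 g/ml ÷ molar mass: 1/16 = 0.0625 mmol/ml; 1/64.5 = 0.0155 mmol/ml.
- Excess of the threshold over that ceiling: 64/0.0625 = 1,024-fold; with 64.5 g/mmol, 64 × 64.5 = 4,128-fold.

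The result does not hinge on the assumed molar mass. For 64 mmol to fit into 1 g, the molecule could weigh at most 1,000 mg/64 mmol = 15.6 mg per mmol, which is far below any protein. No patient can exceed the threshold, so the literal criterion excludes nobody.

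**Step 2: the screening panel against the measurable exclusions.**

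| Exclusion | Supporting test listed at screening |
|---|---|
| INR >2 | INR |
| Platelets <80 × 10^9/l | Platelets |
| QTc >470 ms | Electrocardiogram |
| Low potassium, magnesium or calcium | Potassium, magnesium, calcium |
| Child-Pugh above six points | Bilirubin, albumin, INR (laboratory components) |
| Pregnancy | Urine pregnancy test |
| HbA1c >64 | None |

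HbA1c is the one exclusion with a stated laboratory cut-off whose test is missing from the list. Fasting blood sugar is listed, but no exclusion uses it.

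**Step 3: all listed panels.** HbA1c appears in none of the panels for screening, the sclerotherapy day or follow-up. The week-4 bloods are not itemised, but the withholding rule there uses fasting blood sugar, AST, ALT, bilirubin and amylase, not HbA1c.

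**Step 4: effect on the statistical plan.** The sample size uses a difference of 50 − 29.7 = 20.3 points and an SD of 19.76. By the normal approximation, n per arm = 2 × (1.96 + 0.8416)² × 19.76²/20.3² = 14.9, so 15. With 10% loss, 15/0.9 = 16.7, so 17 per arm and 34 in total, as stated. None of these inputs involves the HbA1c rule.

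**The case against.** **The unit is an obvious slip.** It is probably a typing error for a ratio unit, and no clinician would apply it literally. That is likely, and it limits the practical harm. It remains an error in an operative eligibility rule, and a reader of the article cannot settle the intended unit with certainty.

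**Other criteria catch these patients.** The same list excludes non-malignant illnesses that are uncontrolled, or whose control the study drug may jeopardise, and any condition that the investigator thinks may interfere with the study. Screening includes an extensive medical history and fasting blood sugar. This stands. A reader might infer that patients with uncontrolled diabetes will be randomised and dosed, and the document does not support that. The protection is a matter of judgement, however, and it does not supply the specific definition that the protocol chose to give.

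**The screening list is not a full map of the exclusions.** HIV and uncontrolled hypothyroidism are named as exclusions without a listed test. The diabetes criterion concerns patients already on therapy, whose HbA1c may come from the record, and a journal article is a condensation. This also has force: the text shows that the source of the value is not stated, not that no value was ever obtained. But HIV and hypothyroidism carry no numerical cut-off. The diabetes criterion does, and the other exclusions with a laboratory cut-off have their tests listed.

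**Two stronger readings fail.**

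- *Dilution of the treatment effect.* A reader might argue that each patient stopped after one injection costs the pasireotide arm 20.3/17 = 1.2 points. That assumes no benefit from the first injection. The Discussion puts peak drug level around day 20 after an injection. The first peak is then about 20 − 14 = 6 days after sclerotherapy. The second falls around day 28 + 20 = 48, after the primary endpoint at day 42. The document also gives no count of patients with diabetes. The figure is not supported.
- *Conflict between the withholding rule and the follow-up bloods.* The rule at week 4 uses bilirubin ("AST or ALT >3 × ULN with TB >2 × ULN") and amylase, and neither is listed for weeks 6, 14 and 26. That rule decides only on the second injection, and no dose follows. The two sections do not contradict each other; adding those analytes would be a monitoring preference.

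**Conclusion.** The point holds in a limited form. The HbA1c threshold is wrong as written, by a factor of at least about 1,000 under the molar-mass range and blood density assumed above. Taken literally, this specific criterion excludes nobody. The listed screening assessments do not supply the measurement on which it is defined. Both statements rest on the article alone; the full protocol is not available and may contain the correct unit and test.

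The general exclusion of uncontrolled illness and the medical history lessen the risk without removing the defect. How many patients could be affected cannot be estimated from the document. Sample size, power and the primary analysis do not change. This is a correction that should be made because the drug raises glucose and is given as a depot. It is not a threat to the trial's main comparison.

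**What to change.** Reconcile the sections Exclusion criteria and Screening visit:

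1. Restate the diabetes exclusion with a unit in which HbA1c is reported. The clinical team takes the value and unit from the full protocol; none is proposed here.
2. State where the screening HbA1c value comes from, either by adding it to the screening markers or by saying that a recorded value is accepted.
3. As recruitment started in April 2014, the sponsor should check which unit and which test were actually applied to patients already enrolled, and record the result.

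The cost is one corrected line and at most one further analyte on a blood draw already planned, plus a review of existing screening records. No extra visit or procedure is needed.

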### Trial treatments

#### Aspiration sclerotherapy

All included patients will undergo AS of a single hepatic cyst following standard of care. This single session procedure will be performed by one of our five interventional radiologists, experienced in performing AS. Patients will be admitted the day of AS and will receive intravenous antibiotic prophylaxis (cefazolin 1,000 mg (Eurocept, Ankeveen, the Netherlands) or clindamycin 600 mg (Sandoz, Holzkirchen, Germany) as an alternative in case of allergies). The procedure will be carried out with conscious sedation. Briefly, the cyst will be localized by ultrasonography. Following disinfection and local anaesthesia of the skin, a 5 French pigtail catheter (Cook Medical, Bloomington, United States of America) attached to a three-way tap will be inserted in the hepatic cyst to perform complete fluid evacuation (aspiration). Cyst leakage or communication with vessels or bile ducts will be examined by instillation of contrast medium (Iomeron 300, Bracco Imaging, Konstanz, Germany, up to 20 ml) into the cyst cavity. Contrast medium will then be aspirated from the cyst followed by an injection of 100% ethanol (sclerotherapy). The amount of instilled ethanol consists of 10% of the aspirated cyst volume (up to a maximum of 50 ml). After 10 minutes, ethanol is aspirated and the drain will be removed.

#### Pasireotide

Subjects in the active treatment arm will receive two intragluteal injections of 60 mg pasireotide (SOM230, Novartis, Basel, Switzerland) long-acting release (LAR). The first injection will be administered two weeks prior to AS, the second injection will be administered two weeks following AS. Pasireotide LAR, powder for suspension for injection, is a one-month depot microparticle formulation for intramuscular administration. No dose adjustment is required for race, age, gender, body weight, mild hepatic impairment or renal impairment. The most common adverse events are gastrointestinal by nature and include mild diarrhea, nausea and abdominal pain [18]. These events are more frequent in the first days after treatment initiation and mitigate within time. Moreover, transient hyperglycemia, local injection site skin reactions and headaches are common side effects of pasireotide [18,19]. Previous studies have indicated that pasireotide may prolong the QT interval [20]. Therefore, patients with a prolonged QTc at screening (>470 ms) are not eligible to participate in this study. Known long-term side effects, such as development of gallstones, are not expected in this study given the limited number of injections.

#### Placebo

Patients in the placebo arm will receive two intragluteal injections of 2 ml sodium chloride solution 0.9% (Fresenius Kabi, Hesse, Germany). The first injection will be administered two weeks prior to AS and the second injection will be administered two weeks following AS.

### Study endpoints

#### Primary outcome

The primary outcome of the SCLEROCYST trial is the mean proportional change (%) in cyst diameter of the treated hepatic cyst four weeks after AS, as measured by ultrasound.

#### Secondary outcome

Secondary outcomes are mean proportional change (%) in cyst diameter two, 12 and 24 weeks after AS. Moreover, proportional change (%) in volume, absolute diameter reduction (cm) and rate of cyst recurrence (>80% of original diameter) at follow-up visits will be assessed. In addition, symptoms and health-related quality of life will be measured at baseline, four, 12 and 24 weeks after AS. Finally, any complications or adverse events reported during procedure or follow-up visits will be recorded.

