### Study withdrawal

Subjects can withdraw informed consent and leave the study at any time. The investigator will withdraw a subject from the study for any of the following reasons: pregnancy, consistent failure to adhere to protocol requirements, unacceptable toxicity of study medication, surgical interventions during the study or any other reason if in the best interest of the patient. All data generated up to the time of discontinuation from the study will be analyzed and the reason(s) for discontinuation will be recorded.

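### Recurrence is defined by diameter alone, so a treated cyst that refills and is re-drained between visits can go uncounted as a failure at 12 and 24 weeks

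*Protocol article*

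**What the plan says.** All references are to the protocol article.

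- **Secondary outcome.** Recurrence is given as "rate of cyst recurrence (>80% of original diameter) at follow-up visits will be assessed". The same section lists "mean proportional change (%) in cyst diameter two, 12 and 24 weeks after AS", along with volume and absolute diameter reduction.
- **Follow-up visits.** "Three follow-up visits will be planned at six, 14 and 26 weeks following the first injection", which is 4, 12 and 24 weeks after AS.
- **Background.** Re-intervention is named as a consequence of failed treatment: "strong fluid secretion is associated with lower efficacy rates leading to failure of symptom relief and the necessity to re-intervene".
- **Exclusion criteria.** Percutaneous and surgical treatment are listed as separate things: "Intervention (aspiration with or without sclerotherapy or surgical intervention) within six months prior to baseline".
- **Study withdrawal.** The only intervention on the list of reasons is surgery, followed by a discretionary clause: "unacceptable toxicity of study medication, surgical interventions during the study or any other reason if in the best interest of the patient". For those who leave, "All data generated up to the time of discontinuation from the study will be analyzed".
- **Statistical analysis.** The intention-to-treat set is everyone given one dose or more. The per-protocol set is those who had the two injections, the procedure and every scan. Recurrence is compared by Fisher's exact test.

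No section says how a repeat drainage of the treated cyst is scored.

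**The concern.** Recurrence is one of the two secondary objectives under Study aim. The patients most likely to be re-drained are those whose cyst has refilled with symptoms, which is the failure the endpoint is meant to count. A definition that looks only at diameter on the visit day lets the re-drainage remove the evidence of failure.

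If pasireotide works, more of these patients are in the placebo arm. More failures would then be lost there, and the arms would look more alike than they are. The same scans also feed the 12- and 24-week diameter and volume results, where part of the measured reduction would come from the second drainage.

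**Working it through.** **1. What happens to a re-drained patient under the text**

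| Course after index AS | Recurrence as written |
|---|---|
| Above 80% at a follow-up visit, then re-drained | Counted at that visit. Whether it still counts later depends on whether the rate is cumulative or per visit, which is not stated |
| At or below 80% at every visit so far, refills, re-aspirated between visits, next scan above 80% | Counted |
| Same, but next scan at or below 80% | Not counted; stays in the intention-to-treat set and, if other conditions are met, the per-protocol set |
| Withdrawn for surgery, or under the discretionary clause, before a visit shows more than 80% | Not counted; no later value |

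The last two rows are the defect. The third arises because the Exclusion criteria separate aspiration from surgery, so the surgical withdrawal reason does not cover a repeat aspiration.

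**2. The plan's own figure, as a check on the inputs**

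Sample size considerations gives a 29.7% reduction (SD 19.76) with AS alone, a 50% target, 80% power and α 0.05, so the difference is 20.3 points. By the normal approximation:

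n = 2 × [19.76 × (1.960 + 0.842) / 20.3]² = 14.87, so 15 per arm; 15 / 0.90 = 16.7, so 17 per arm and 34 in total.

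This agrees with the article. No stated figure is in dispute.

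**3. Illustration of size**

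Assumptions not in the article: normal distribution, the same SD in both arms, and four-week values carrying over to later visits. A diameter above 80% of original is a reduction below 20%.

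- Placebo: Φ((20 − 29.7)/19.76) = Φ(−0.49) = 31.2%, or 5.3 of 17
- Pasireotide: Φ((20 − 50)/19.76) = Φ(−1.52) = 6.4%, or 1.1 of 17
- Difference: 24.7 points

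Let m be the share of recurrences, equal in both arms, that are re-drained and scored as non-recurrent. The recorded difference is 24.7 × (1 − m). Power is by exact enumeration of Fisher's test at 17 per arm.

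| m (assumed) | Recorded difference | Power |
|---|---|---|
| 0 | 24.7 points | 32% |
| 25% | 18.5 points | 19% |
| 50% | 12.4 points | 7% |
| 75% | 6.2 points | 0.6% |

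**4. Counts**

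- One hidden placebo recurrence can move the test across 5%: 7/17 against 1/17 gives p = 0.039; 6/17 against 1/17 gives p = 0.085.
- Both routes lose failures. Take 5/17 = 29.4% in the placebo arm. If two are re-drained and scored non-recurrent, 3/17 = 17.6%. If the two are withdrawn and leave the denominator, 3/15 = 20.0%.

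**5. Direction**

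The recorded difference is too small when the placebo share hidden times 31.2% exceeds the pasireotide share hidden times 6.4%. To reverse that, the share hidden under pasireotide would have to exceed 0.3118/0.0645 = 4.8 times that under placebo. This ratio rests on the same model as step 3.

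**6. Mean diameter at 12 and 24 weeks**

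One re-drained patient whose apparent reduction rises by an assumed 20 to 40 points moves an arm mean of 17 by 20/17 = 1.2 to 40/17 = 2.4 points. This should not be set against the 20.3-point design difference, which belongs to the four-week endpoint.

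**The case against.** The strongest reply is that this is silence in a condensed article, and that a full protocol or analysis plan could say how rescue is handled. That stands for the treatment of post-rescue scans. It does not dispose of the recurrence endpoint, whose definition is stated here and misclassifies such a patient if followed.

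Several further objections stand and limit the point:

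- A reader might infer that a re-aspirated patient always remains in the study. The text does not settle this, because the discretionary withdrawal clause could be used. The failure is then lost by the other route.
- A reader might infer that every re-drained failure is scored as a success. A patient above 80% at an earlier follow-up visit can be captured there. The Background also calls re-accumulation transient, so the exposed group may be small.
- A reader might infer that prior aspiration is excluded because it alters the cyst. The Exclusion criteria give no reason; they show only that aspiration and surgery are treated as distinct.
- A reader might extend the point to somatostatin analogues started in follow-up. Nothing suggests that this is expected, so it is at most a missing detail.
- Analysing observed diameters regardless of rescue is a legitimate treatment-policy choice, and carrying forward the last pre-rescue value is itself debatable. This is why the fix does not require it.

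**Conclusion.** The point holds for recurrence at 12 and 24 weeks. As defined, the endpoint can miss a failure that was re-drained between visits or withdrawn for re-intervention, and the likely effect is bias towards no difference. That direction assumes that failures are commoner on placebo and that the share hidden does not differ greatly between arms.

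The size cannot be established, because the article gives neither a re-intervention rate nor a late recurrence rate. The fall from 24.7 to 18.5 or 12.4 points is an illustration under stated assumptions. Even with nothing hidden, power for recurrence is only about 32% under that model, so the main damage would be to the estimate.

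The results do not call the four-week primary endpoint into question. It is little exposed, although no stated rule protects it. The definition should be changed, but the trial's main conclusion does not depend on it.

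**What to change.** 1. Define recurrence as a diameter above 80% of original at a follow-up visit, **or** any re-intervention on the treated cyst after the index AS (aspiration, alone or with sclerotherapy, or surgery). Count it from that date onward, and include patients withdrawn because of it.
2. Flag diameter and volume values taken after a re-intervention. Report the 12- and 24-week results with and without them as a sensitivity analysis, with no requirement to carry the last value forward.
3. Reconcile Exclusion criteria, Secondary outcome, Study withdrawal and Statistical analysis on how re-intervention is scored.

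The cost is a change of wording and one item on the case report form recording date and type of re-intervention. There are no extra patients or visits, and N stays at 34. The small downside is that the composite includes a clinician's decision, although one made while blinded. The change should be settled before unblinding. It concerns scoring only and does not alter what treatment a patient may receive.
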